Several promising reports concerning DBS in patients suffering from SE-AN have been published (23–31). In particular, the seminal studies by the group of Toronto showed that surgery and DBS are well tolerated in this population (28, 29). Nevertheless, these previous studies present some limitations. First, the DBS target was not systematically designed for AN. Second, included patients had frequently a very low body mass index (BMI). The BMI increase should not be the only studied endpoint since medical treatment alone cand lead to an acceptable BMI in AN (32–35). BMI is influenced by many variables other than pathophysiological improvement in the subpopulation of patients with SE-AN. Repetitive inpatient treatment can temporarily increase or stabilize BMI without quality of life improvement. While BMI at discharge remains a well-characterized prognostic factor (36, 37), recent studies have highlighted the need for a harm reduction-based treatment (38). Pilot studies assessing treatment acceptability and tolerability are necessary to explore the possibility of a subsequent larger, randomized, trial (39, 40).

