1. Presence of Anorexia nervosa according to DSM V criteria. 2. Age 18 to 65 years. 3. Chronic, treatment-resistant anorexia nervosa, defined as:
- Anorexia nervosa evolving for at least 7 years - Inability to maintain a BMI ≥ 17kg/m² for 2 months following hospitalization in a specialized center for the management of patients suffering from eating disorders (abiding to the criteria of the French Federation Anorexia Bulimia and the General Directorate of Healthcare [Direction Général de l’Offre de Soins]). Failure of at least 2 hospitalizations in a specialized center during the history of the disease. - Inability to maintain a BMI ≥ 17kg/m² for more than 3 consecutive months during the year preceding the inclusion, while following an outpatient treatment conducted by a specialized center for the management of patients suffering from eating disorders (abiding to the criteria of the French Federation Anorexia Bulimia and the General Directorate of Healthcare [Direction Général de l’Offre de Soins]). Failure of at least 2 outpatient treatments conducted by a specialized team during the history of the disease
4. Impaired psychological, social, and occupational functioning defined by a score ≤ 45 on the Global Assessment of Functioning Scale. 5. Anorexia nervosa is judged to be the primary disorder if there are psychiatric comorbidities such as depression, anxiety disorder, obsessive-compulsive disorder, or personality disorder, by at least two independent experts. 6. The patient is able to comply with the operational and administrative requirements of the study and is able to complete the protocol questionnaires. 7. Patient provides written informed consent. 8. Patient is drug-free or on a medication that has been stable for at least 6 weeks at the time of the study entry. 9. If female subject and of childbearing age: use of an effective method of contraception. 10. Patient has health insurance.
Exclusion Criteria

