##### DBS efficacy

2.4.2.1

For the measurement of DBS efficacy, we rely on:

Duration of hospital stays in a specialized center. Comparison between the two years before inclusion in the STIMARS protocol and the two years after inclusion (with a 6-month washout interval right after the DBS surgery to consider stimulation start and initial parameter adjustments).BMI monitoring in a standardized way. Monthly measurements during the follow-up according to the calculation rule: weight (kilograms)/height² (square meter) during each follow-up visit with the referring physician. Comparison between the two years before inclusion and the two years after inclusion (with a 6-month interval to consider stimulation start and first parameter adjustments). Additionally, body composition will be assessed by multifrequency impedancemetry Z-Métrix^®^ (Bioparhom). Resting energy expenditure will be measured by indirect calorimetry with Omnia 1.6.10 - Quark RMR (COSMED).Changes in preoperative and postoperative scores on the various clinical dimensions of AN via various questionnaires (see **Table 3**). Eleven dimensions of eating disorders will be measured by the *Eating Disorder Inventory-2* (EDI-2) (47). Levels of anxiety and depression will be assessed through the *Hospital Anxiety and Depression* Scale (48). The presence and severity of obsessive-compulsive disorder will be measured through the *Yale-Brown Obsessive Compulsive Scale* (Y-BOCS) (49, 50). These data will be collected during the preoperative, early postoperative, and late postoperative neuropsychological assessments (3 months, 12 months, and 23 months after inclusion, respectively). Additionally, the Zarit scale aims to evaluate the burden of the patient’s severe and resistant anorexia nervosa on a caregiver: the caregiver present at the inclusion visit must be 1) present during the patient’s neuropsychological assessments or 2) available by telephone to complete the scale (duration of the interview: 15 minutes, including 5 minutes for completing the scale).Changes in neurocognitive dimensions. All cognitive tasks will be performed on computers (with MATLAB^®^) under the supervision of a trained neuropsychologist.Changes in pupillometry assessments (**Figure 1**). Pupillometry measures the pupil diameter for an objective evaluation of the emotional impact of a task on the subject. The pupil dilates in response to positive and negative emotions, as well as in response to light. Using a subtractive method, the effect of light is removed and the emotional impact is quantified. We use pupillometry (dedicated eye tracker, chin rest, and a dedicated computer; see **Figure 1**) to comparatively assess the emotional impact caused by 60 computer-viewed pictures belonging to different types of stimuli: 12 neutral images (e.g. image of a book), 12 negative images (e.g. a violent image), 12 pleasant images (e.g. image of babies, kittens), 6 images of caloric foods (e.g. image of ice cream), 6 images of lean food (e.g. image of carrots), and 12 images of standardized silhouettes depicting different BMI. Emotional stimuli (neutral, pleasant, and negative images) were taken from the International Affective Picture System (IAPS) (51). Food pictures come from the Open Library of Affective Foods (52). Standardized silhouettes were computer-generated pictures (53), representing a naked woman (height 165 cm) varying in BMI, with underweight silhouettes (BMI: 12–16 kg/m2), normal weight silhouettes (BMI: 19–23 kg/m2) and overweight silhouettes (BMI: 26–30 kg/m2). All pictures are in grey levels, 8 bits, 1024x768px, modified with TheGIMP^©^. The task was programmed using MATLAB^®^. Stimuli were randomized into 12 blocks. Each block containing five pictures: three IAPS pictures (one positive, one negative, one neutral), one food picture, and one standardized silhouette. Each picture will be shown for 6s with a 2s in‐between fixation point. The quantitative aspect of the emotional impact is given by the changes in pupil diameter, unlike the sign of the emotion (positive or negative) which requires an additional questionnaire: at the end of the task, subjects will view the pictures a second time and will be asked to evaluate valence and emotional arousal, using a simple numeric scale. Questions will be ‘Would you rate this image as pleasant or unpleasant?’ from 1 (very unpleasant) to 9 (very pleasant), and ‘What is the emotional impact, how powerful is the feeling caused by this picture?’ from 1 (very low) to 9 (very high).Time specificities (capacity to delay reward) will be measured through the Delay Discounting Task (DDT). In the DDT, subjects are presented with two options of various amounts of money available at different delays: one smaller amount of money but available within a shorter delay (“Smaller Sooner”, SS) and one larger amount of money but available in a longer delay (“Larger Later”, LL). This task allows measuring the subjective value that a person perceives in a given reward depending on the delay.Cognitive flexibility will be measured through the Brixton test (54, 55), the Trail-Making Test (56) and the Wisconsin Card Sorting Test (57). Previous research suggests that this test has no practice effect (58).The Slip-of-action Task (SOAT) (59, 60) will assess reward-motivated versus habit-driven behavioral choices. The task is detailed in a previous publication (18) and measures the tendency to lose sight of a goal (goal/reward-motivated choices) due to the activation of habitual responses (habit-driven choices).

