## Discussion

3

Patients suffering from treatment-resistant AN have limited treatment options nowadays. They exhibit poor outcomes, even in expert centers (71). Our study protocol aims to support the growing literature on DBS for treatment-resistant AN.

Costs associated with AN are mostly related to hospital stays (72). The average length of stay for patients with AN is higher than 100 days in Europe (73). During hospitalization in expert centers, refeeding approaches lead to a clinical remission according to the BMI, even with higher-calory refeeding (74). However, relapse of AN arises frequently during the 18 months after hospitalization (75). This underlines the need to manage more community-oriented therapeutic approaches in AN patients. Our study does not require very low BMI to include the patient: the aim is more to manage the deinstitutionalization of AN patients than to obtain weight gain.

Whereas the safety of DBS is now well-established in neurological conditions, this question remains for treatment-resistant AN patients (76, 77). This study will help to refine the expected complication rate in front of these malnourished patients. Moreover, DBS is reversible and customizable. These two points explain why DBS, a reversible neuromodulation technique, should always be considered rather than irreversible lesion techniques (such as thermolesions, radiosurgery) in psychiatric patients.

The main limitations of this study are the single arm and open-label characteristics. This study design has been considered as mandatory by the French authorities. After confirmation of the DBS safety in patients with treatment-resistant AN, a larger study will be possible. The small study sample is in line with the main outcome of safety. We have decided to monitor the patient’s quality of life with two scales translated and validated in French, to minimize the common misgrading of quality of life in anorexia nervosa patients (78). However, these scales are generic and an eating disorder-specific measure would represent a nice to further studies (79). The measurement of healthcare intervention acceptability should investigate multiple aspects: despite numerous psychiatric follow-up visits, only limited data will be collected during the protocol (62). The development of a specific theory-informed questionnaire about DBS for SE-AN would have been a significant improvement and should be done for the next studies (80, 81).

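### The before/after BMI comparison does not separate weights taken in hospital from weights taken in the community, so a change in BMI can partly reflect a change in inpatient time

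*Protocol article*

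**What the plan says.** Section 2.4.2.1 (DBS efficacy) defines the BMI endpoint as "BMI monitoring in a standardized way. Monthly measurements during the follow-up according to the calculation rule", with the weight taken "during each follow-up visit with the referring physician". The contrast is a "Comparison between the two years before inclusion and the two years after inclusion (with a 6-month interval to consider stimulation start and first parameter adjustments"). The item just before it in the same list is "Duration of hospital stays in a specialized center", compared over the same windows with a similar 6-month exclusion.

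Section 2.5 (Participant timeline) and Table 4 require BMI at least monthly during follow-up. Visits may be more frequent where care requires it, and no exemption is given for a patient who is in hospital. The source of the weights before inclusion is not stated. Section 2.8.2 (Statistical analysis) names paired tests, repeated-measures ANOVA or Wilcoxon for quantitative data, and none of these carries a term for admission.

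The protocol's own view of BMI is in three places:

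- Section 1.1: "Repetitive inpatient treatment can temporarily increase or stabilize BMI without quality of life improvement", and "BMI is influenced by many variables other than pathophysiological improvement in the subpopulation of patients with SE-AN".
- Section 3 (Discussion): "During hospitalization in expert centers, refeeding approaches lead to a clinical remission according to the BMI". The same paragraph gives an average European stay of more than 100 days and says that the trial aims at less institutional care more than at weight gain.
- Table 1, inclusion criterion 3, makes care setting part of the definition of treatment failure: "Inability to maintain a BMI ≥ 17kg/m² for 2 months following hospitalization in a specialized center", and a parallel condition for outpatient treatment.

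**The concern.** The protocol says that admission can move BMI without the patient's quality of life improving. It then defines a BMI outcome that ignores admission, in a trial that hopes to change how much time patients spend in hospital. A patient who stays at home after surgery loses any refeeding peaks that were in the earlier window. A patient who is readmitted more often adds peaks to the later one. The before/after difference then mixes a possible effect of stimulation with a change in inpatient time, and the planned analysis cannot separate them.

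The entry criteria take care setting into account, but the outcome does not. This matters even in a pilot, because the abstract promises an effect-size estimate for planning larger trials. With 12 patients, altered admission patterns in a few of them can move the BMI figure that is carried forward.

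**Working it through.** The protocol states no expected BMI change, standard deviation or power for BMI, so there is no planned figure to reproduce. The sample size of 12 does not rest on BMI.

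**Do inpatient weights enter the comparison?** For follow-up, the text implies that they can. BMI is due at least monthly, no exemption for admitted patients is given, and a 100-day stay spans about three monthly measurements (100/30.4 = 3.3). For the period before inclusion, the text does not settle it.

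**Inputs for the illustration**

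- Window before: 2 years = 730 days (section 2.4.2.1).
- Window after: 2 years less 6 months = 730 − 182.5 = 547.5 days (same section).
- Length of stay: 100 days, taken from the Discussion's average of more than 100.
- Number of stays in each window: assumed.
- Inpatient minus community BMI gap: not in the document; assumed 1, 2 and 3 kg/m².
- Summary measure: mean BMI over the window, with inpatient weights included in both windows; assumed.

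**Formula.** With f the share of a window spent in hospital, mean BMI = f × inpatient BMI + (1 − f) × community BMI. If both levels stay constant, the artefact in the before/after difference is

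(f after − f before) × gap.

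**Results**

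| 100-day stays before → after | f before | f after | Gap 1 | Gap 2 | Gap 3 |
|---|---|---|---|---|---|
| 2 → 0 | 200/730 = 0.274 | 0 | −0.27 | −0.55 | −0.82 |
| 1 → 0 | 100/730 = 0.137 | 0 | −0.14 | −0.27 | −0.41 |
| 0 → 1 | 0 | 100/547.5 = 0.183 | +0.18 | +0.37 | +0.55 |
| 1 → 2 | 0.137 | 200/547.5 = 0.365 | +0.23 | +0.46 | +0.68 |

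**When the sign reverses.** In the 2 → 0 case no inpatient time remains after surgery. A true community gain therefore adds in full to the later mean, and a gain above 0.27, 0.55 or 0.82 kg/m² (for gaps of 1, 2 or 3) produces a net rise. The artefact then shrinks the apparent benefit but does not hide it.

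**The case against.** The strongest reply is that the concern rests on silence. The article does not say that inpatient weights are used, it does not name a window mean, and a rule on admissions could stand in the full protocol or the analysis plan. In part this is right: inclusion of inpatient weights before surgery is unproven, and so is any suggestion that those records are denser during admissions. But the article does fix the measure, the visits, the windows and the one interval to be removed. Applied as written to the follow-up visits, that definition does not separate settings.

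A reader might infer several stronger things that the documents do not support:

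- That success at avoiding admission necessarily lowers BMI and readmission necessarily raises it. This holds only if community BMI is unchanged. Improved patients may gain weight at home, and low weights before a readmission also enter the comparison.
- That admission is said to raise BMI with no benefit at all. The Background says only that it can temporarily raise or stabilise BMI, and the missing benefit it names is in quality of life.
- That patients spent much of the earlier window in hospital. Criterion 3 asks for two failed admissions at any time in an illness of at least 7 years.
- That BMI is a leading endpoint. It is one of several secondary measures, nothing ranks it, the Background cautions against relying on BMI alone, and section 2.8.1 says that effectiveness is not being evaluated.
- That BMI should be restricted to community weights, perhaps also dropping the 2 months after discharge. That would selectively remove time from patients who relapse, and criterion 3 judges exactly those 2 months.

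Hospital days are also reported over the same windows, so readers could see whether the two moved together. That helps, but it does not show how much of a BMI change came from inpatient time.

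**Conclusion.** The concern holds in a limited form. The BMI comparison is not separated by care setting, although the protocol itself says that setting can move BMI and the trial aims to change time in hospital over the same windows. A before/after difference can therefore partly reflect altered inpatient time, and neither its sign nor its size can be attributed to stimulation without knowing the setting.

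The illustrated size, −0.27 to −0.82 kg/m² for two stays before and none after, rests wholly on the assumed gap, stays and window mean. It shows a plausible order of magnitude and is not an estimate for this trial. The point does not touch the primary safety endpoint or the sample size. It is a worthwhile, inexpensive improvement to one secondary endpoint.

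**What to change.** In the definition of the BMI endpoint and its analysis:

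1. Flag each BMI as inpatient or community, using the hospital-stay records needed for the first efficacy endpoint.
2. Use one value per calendar month in both periods, chosen by a rule set in advance, so that more frequent visits in difficult months do not add weight.
3. Report the before/after comparison for community weights beside the all-weights comparison, with the number of inpatient months per patient and period.
4. Add a responder measure that mirrors inclusion criterion 3: BMI ≥ 17 kg/m² held for more than 3 consecutive months in outpatient care, with months in hospital not counting as success.

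Keep the all-weights result, and do not drop the 2 months after discharge.

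The cost is a change of wording and some derivation work. The flag needs admission and discharge dates, whereas the article mentions only the duration of stays, and stays outside specialized centres would have to be recorded too. Patients with many admissions will contribute fewer community values. For weights before inclusion, information on setting may be limited, and its completeness should be reported.

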
**Figure 1 f1:**
[figure not shown]
Details of the pupillometry. **(A)** the pupillometry set-up with a chin rest, a computer with a 21″ screen, and an eye tracker; **(B)** the eye tracker (LiveTrack Fixation Monitor, Cambridge Research Systems Ltd, UK); **(C)** the first step is to calibrate the camera for pupil tracking during test; **(D)** different image sets are proposed in random order (neutral images, violent images, sexual images, different silhouette images) with a washout image (a black spot, see middle image) between each test image; **(E)** different pupil sizes. Pupillometry was performed in a windowless room with low luminosity.

**Table 3 T3:** Details of neurocognitive assessment.

Anorexia Nervosa Dedicated Form
1. the Eating Disorder Inventory 2
Psychiatric Forms
1. Hospital Anxiety and Depression Scale 2. Yale Brown Obsessive-Compulsive Scale 3. Scale for Suicide Ideation
Neurocognitive Forms
1. Montreal Cognitive Assessment 2. Delay Discounting Task 3. Wisconsin Card Ranking Test 4. Brixton Test 5. Trail Making Test A and B 6. Slip-of-action test 7. Habits vs Goal Directed Behavior test 8. Dubois Five Word Test 9. Rey/Taylor Figure
Quality of life Forms
1. SF-36 Quality of Life Questionnaire 2. Global Assessment of Functioning Scale
Care-taker Form
1. Zarit Burden Inventory (to be completed by the care-taker)

###### DBS acceptability

2.4.2.1.1

In this study, the DBS acceptability of the method is measured via simple objective numerical measures (percentage of patients who accepted inclusion, percentage of patients who completed the study, percentage of patients willing to repeat the DBS procedure if necessary) and more complex criteria which are sought during follow-up consultations (61). The criteria sought during follow-up consultations are those described in the Theoretical framework of acceptability: affective attitude, burden, ethicality, intervention coherence, opportunity costs, perceived effectiveness, and self-efficacy (62).

##### Local field potential recording during an exposure task

2.4.2.2

**Figure 2** summarizes NAc LFP recording.

**Figure 2 f2:**
[figure not shown]
Details of the local field potential recording during an exposure task. **(A)** the leads are externalized after the surgery. Two days after the surgery, the extensions are connected to an electroencephalogram amplifier, and then to two computers, one for the signal analysis and the other one for the exposure task. **(B)** the exposure task consists in presenting 120 stimuli. From left to right: each stimulus will be composed of a fixation point (random time from 1 to 2 sec), followed by the image (5 sec), followed by two scales on which the patients will have to rate the induced level of distress and the arousal of the image (visual analog scales from 0 to 5, random order of scale presentation, maximum time for the ratings of 10 sec), followed by a blank screen (random time from 2 to 4 sec).

We optionally propose patients perform LFP recordings in the NAc during an exposure task, based on individualized symptoms-related stimuli. If a patient agrees to perform this procedure, the surgery is two-staged (see above).

###### Stimuli

2.4.2.2.1

During the exposure task, four types of stimuli are used: individualized- and generic- symptoms-related, and neutral pictures. Individualized stimuli are obtained by asking the patient to take pictures in his or her environment during the month before surgery. Generic stimuli, selected from a dedicated database, are added to increase the number of trials and the signal-to-noise ratio. Symptoms-related pictures are typically scales, body images, and sweet/high-calorie foods while neutral pictures are random objects or landscapes. All stimuli are normalized for luminance and contrast.

###### Task

2.4.2.2.2

Pictures are presented in blocks of 15 trials. Each trial is composed of a fixation point (random time from 1 to 2 sec), followed by the image (5 sec), followed by two scales on which the patient has to rate the induced level of distress and the arousal of the image (visual analog scales from 0 to 5, random order of scale presentation, maximum time for the ratings of 10 sec), followed by a blank screen (random time from 2 to 4 sec). In total, 120 stimuli are presented during the task.

